### **6.3.2 Blinding Procedures**

The study format is double-blind in the sense that neither will the discharging HPs know which of the two interventions they provide nor will the patients know whether they receive the verum or the control intervention. Both HPs and patients will be informed that the trial aims at studying and improving the procedures at and after hospital discharge of multimorbid patients, but they will be unaware of procedural details pertaining to the study arm to which they do not belong.

The non-blinded investigators and the biometrician at the study center will not be involved in measuring outcomes.

## **6.4 Unblinding Procedures (Code break)**

An emergency code break will be available to the investigators at the study center. This code break should be opened only in emergency situations when the identity of the investigational intervention must be known to the investigator in order to provide appropriate medical treatment. However, since the patients' clinical history files will contain all relevant medical information including, in particular, any changes of the patients' medication plans, we do not expect the necessity of unblinding to occur except in the event of adverse events (AEs) in the intervention group leading to early termination of the study. In this case, all participants would be unblinded and the HPs informed about their study group affiliation.

## 7 STUDY POPULATION

### 7.1 Eligibility Criteria

We focus on chronically ill, multimorbid patients in hospitals of all types, levels and legal structures in northern, eastern and central Switzerland.

#### 7.1.1 Inclusion Criteria

A prescription of five or more drugs is considered a characteristic for multimorbidity. Multimorbid elderly patients incapable of judgement (e.g. patients with dementia) are a clinical reality and should therefore be included in our study for increased representativity. Moreover, like any other patient they can personally benefit from prolonged readmission times, the result hoped for from our study intervention.

Based on this rationale, patients fulfilling all of the following inclusion criteria may be enrolled in the study:

##### Inclusion criteria:

- In-hospital patient at the time of inclusion
- Male or female of 60 years or older with five or more drugs prescribed
- Signed informed consent or – in case of a patient incapable of judgement – fulfillment of the criteria laid down in HFG Art. 24, 1a.-c. with a legal representative according to ZGB Art. 378

#### 7.1.2 Exclusion Criteria

Hospitals who took part in the Swiss national pilot project “progress! Sichere Medikation an Schnittstellen” will not be considered for participation in the study (but may be involved in the pilot test). On the patient level, any one of the following exclusion criteria will lead to exclusion from the study:

##### Exclusion criteria:

- End-stage disease with a life expectancy below three months
- Cognitive inability to follow study procedures neither independently nor with assistance

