| Study Design:                 | Single-center double-blind cluster-randomized parallel-controlled clinical trial with a 6-month follow up.                                                                                                                                                                                                                                                                                                                                                                                                                                                                                                                                                                                                                                                                                                                                                                                                                                                                                                                                                                                                                                                              |
| Inclusion/Exclusion Criteria: | 
Inclusion criteria: In-hospital patients will be eligible if they are 60 years or older and prescribed 5 or more drugs.
 
Exclusion criteria: Cognitive inability to follow study procedures or end-stage disease with a life expectancy of less than 3 months.
                                                                                                                                                                                                                                                                                                                                                                                                                                                                                                                                                                                                                                                                                                                                                                                                                                                                                             |

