## **2.7 Participant Privacy and Confidentiality**

The investigators are liable to treat the entire information related to the study and the compiled data strictly confidentially. Anonymity is warranted in publications and public presentations. Any passing-on of information to persons that are not directly involved in the study must be approved by the owner of the information.

Data generation, transmission, archiving and analysis of personal data within this study strictly follow the current Swiss legal requirements for data protection. Prerequisite is the voluntary approval of the participant given by signing the informed consent prior start of participation of the clinical trial.

Individual participant medical information obtained as a result of this study is considered confidential and disclosure to third parties is prohibited. The participants' confidentiality will be further ensured by utilizing participant identification code numbers to correspond to treatment data in the computer files.

Such medical information may be given to the participant's personal physician or to other appropriate medical personnel responsible for the participant's welfare, if the patient has given his/her written consent to do so.

Data generated as a result of this study will be available for inspection on request by the monitors and by the CEC.

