### 7.2 Recruitment and Screening

For the adequate number of HPs and patients to be included in the trial see the sample size calculations in section 11.2.

Different hospitals – including but not limited to the Kantonsspital Baden, Kantonsspital Glarus, Kantonsspital Graubünden Chur (medical clinic), See-Spital Horgen, Spital Lachen, Spital Limmattal Schlieren, Spital Linth Uznach, Spital Männedorf, Kantonsspital Münsterlingen, Spital Muri, Spital Schwyz, Kantonsspital St. Gallen, Stadtspital Triemli Zurich, Stadtspital Waid Zürich, Kantonsspital Winterthur (polyclinic, surgical ward), Spital Zollikerberg, UniversityHospital Zurich (clinics for gastroenterology, pneumology and geriatrics) – will be contacted on the medical management level with detailed written information about the study and an invitation to participate. Should the targeted number of senior HPs be missed due to a low response rate, remainders will be sent out. If, on the other hand, the response exceeds the actual demand then a random selection of senior HPs will be drawn and the remaining respondents will be waitlisted to compensate for potential withdrawals.

The in-hospital recruitment of patients will be performed by HPs and/or nurses; a person responsible for recruitment will be defined in every clinic or ward. The patients' life expectancies and cognitive abilities will be assessed as part of the recruitment process. Patients will be recruited during four months or until the envisaged number of participants per cluster (senior HP) is reached, and follow up will last for six months for each patient.

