## 8 STUDY INTERVENTION

### 8.1 General Information and Administration of Interventions

#### 8.1.1 Study Intervention

The intervention takes place on different levels with different target populations:

- a. *Teaching session (“Teach-the-Teachers”) for the senior HPs in charge of postgraduate training and supervision of the interns (assistant physicians)*

The purpose of this training of two hours duration is to integrate the discharge procedure (see below) into the daily work of the HPs during the study period. Consecutively, the senior HPs will teach the interns how to apply the structured discharge procedure. This will guarantee the consistency of the intervention even if the fluctuation among interns is high due to organized job rotations within hospitals.

The teaching session will address the following items:

- How to identify patients eligible (possibly in collaboration with nurses)
- How to handle the in- and exclusion criteria
- How to apply the medication review tool (discharge checklist in forms 5b and 5c, see list of study instruments in appendix 18.1) which has been previously tested (15, 32) to the medication plan of the patient before discharge by the HP
- How to involve the senior HP responsible for the interns’ supervision in the medication review, depending on the clinic’s/wards’ usual discharge procedures
- How to involve patients in the changes suggested by the HP
- How to create a discharge medication plan for the patient, after the decision is taken
- How to involve the GPs in the post-discharge phase. An offer for the GP to call the HP in order to discuss the medication plan is prepared on the discharge medication plan. This should guarantee a consensus between HP and GP in order to increase the GPs’ adoption of the changes suggested on the long term
- How to deal with the different data collection forms

- b. *The intervention at discharge*

The intern HP performs a critical review of the medication plan, supervised by his senior HP, discusses the results of this review and his suggestions with the patient and creates a discharge medication plan to be used by the patient. The patient is encouraged to consult his GP within seven days.

Furthermore, the intern HP communicates all medication changes (cessation of specific medication, change of dosage, introduction of new drugs) to the patient’s GP in written form, accompanied with an invitation to the GP to discuss any medication changes (forms 5b and 5c, see appendix 18.1).

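### The synopsis and sections 2.6/2.7 do not match the eligibility and consent rules of section 7.1 for cognitively impaired patients, and the cognitive exclusion rests on undefined study procedures that ward staff judge after allocation

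*Protocol*

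**What the plan says.** **Who is eligible.** The synopsis lists as exclusions "Cognitive inability to follow study procedures or end-stage disease with a life expectancy of less than 3 months". It mentions neither assistance nor a representative. Section 7.1.1 takes the opposite line: "Multimorbid elderly patients incapable of judgement (e.g. patients with dementia) are a clinical reality and should therefore be included in our study". The inclusion criteria give the consent route, "in case of a patient incapable of judgement – fulfillment of the criteria laid down in HFG Art. 24, 1a.-c. with a legal representative". Section 7.1.2 then excludes for "Cognitive inability to follow study procedures neither independently nor with assistance". The double negative is garbled; the evident meaning is that a patient is excluded only if unable to follow procedures both alone and with help.

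**Who signs.** Section 2.6 describes a participant who reads, signs and dates the form. Section 2.7 adds: "Prerequisite is the voluntary approval of the participant given by signing the informed consent prior start of participation of the clinical trial". Neither section mentions a representative.

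**Who judges cognition, and when.** Section 7.2 says "The patients' life expectancies and cognitive abilities will be assessed as part of the recruitment process", by hospital physicians or nurses on the ward. Section 6.1 places patient recruitment after the senior physicians' training, which itself follows randomization. Section 6.3.2 says physicians will not know the procedural details of the other arm.

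**What the procedures are.** In the intervention arm the intern "discusses the results of this review and his suggestions with the patient and creates a discharge medication plan to be used by the patient" (section 8.1.1). In the control arm discharge is usual care (sections 8.1.2 and 9.3.4). At 1, 3 and 6 months, sections 9.3.5 to 9.3.7 list the same tasks with no difference by arm.

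**The concern.** Two things are at stake.

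The first is consistency. If the protocol gives two answers on patients who need help, wards may enrol them or not according to the text they follow. The representativeness that section 7.1.1 gives as its reason for including them could then be lost.

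The second is comparability of the arms. In a cluster trial that recruits after allocation, a loosely defined exclusion is one route by which the arms can come to hold different patients. Intervention staff are taught eligibility in the same session as the review tool and patient involvement (section 8.1.1), so they might count the drug discussion among the procedures a patient must follow. Control staff know of no such discussion. If intervention wards excluded more impaired patients, and those patients were readmitted sooner, the primary outcome would show an apparent benefit. The model could not correct for this: the patient characteristics collected are age and sex (sections 9.2.3 and 9.3.3), and the Cox model uses these plus the allocation covariates (section 11.3.2).

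**Working it through.** **Step 1: the texts applied to one patient.** Take a patient with dementia who can follow the procedures only with a relative's help and who has a legal representative.

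| Source | Result |
|---|---|
| 7.1.1, intent and inclusion criteria | Eligible, through the representative |
| 7.1.2 | Not excluded, because assistance suffices |
| Synopsis, as written | Excluded if unable to follow procedures unaided; assistance not mentioned |
| 2.6 and 2.7, as written | No route to consent except the participant's own signature |

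The missing assistance clause changes the answer for this patient.

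**Step 2: is the criterion the same in both arms?** On paper, yes: there is one text, both arms are taught it (sections 3.5 and 8.1.1), and one checklist is listed (form 11a, section 18.1). Its yardstick is undefined, however. Tasks at discharge differ by arm, and the assessors act after allocation knowing only their own arm. Uniform application is intended but not secured.

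**Step 3: how large could a difference be?** No figure in the protocol is in dispute, and the protocol gives neither the share of impaired patients nor their readmission risk. What follows is an illustration.

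Inputs from section 11.2: control median 92.7 days and planned hazard ratio 0.80. The daily hazard is λ = ln 2 / 92.7 = 0.00748. As a check, 1 − exp(−0.00748 × 30) = 20.1%, the protocol's own 30-day rate.

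Assumptions: no true effect; λ applies to unimpaired patients; impaired patients have hazard h × λ; follow-up T = 182 days.

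Per patient, expected events are 1 − exp(−hλT), and expected days at risk are that number divided by hλ:

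| Group | Events | Days at risk |
|---|---|---|
| Unimpaired (h = 1) | 0.7436 | 99.44 |
| Impaired, h = 1.5 | 0.8701 | 77.58 |
| Impaired, h = 2 | 0.9342 | 62.47 |

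*Scenario A: 20% impaired, h = 1.5, half of them excluded in the intervention arm only.*
- Control: events 0.8 × 0.7436 + 0.2 × 0.8701 = 0.7689; days 0.8 × 99.44 + 0.2 × 77.58 = 95.07; rate 0.00809.
- Intervention: impaired share 0.10 / 0.90 = 11.1%; events 0.7576; days 97.01; rate 0.00781.
- Ratio 0.966.

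*Scenario B: 30% impaired, h = 2, all excluded in the intervention arm only.*
- Control: events 0.7 × 0.7436 + 0.3 × 0.9342 = 0.8008; days 0.7 × 99.44 + 0.3 × 62.47 = 88.35; rate 0.00906.
- Intervention: rate 0.00748.
- Ratio 0.825.

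The large-sample Cox hazard ratio for the same mixtures is 0.966 and 0.826, so about 0.97 and 0.83. On the log scale that is ln(0.966)/ln(0.80) = 16% and ln(0.826)/ln(0.80) = 86% of the planned effect.

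**The case against.** **The synopsis is only a summary.** It also omits the consent criterion and the hospital-level exclusion, and recruiters work from checklist 11a, whose text is not shown. This is fair as far as it goes, but a summary that drops a qualifier deciding eligibility still needs correcting. A reader might infer that the synopsis shuts out all cognitively impaired patients. It does not: it excludes inability to follow study procedures, which is not the same as incapacity of judgement. The conflict concerns patients who can follow procedures only with help.

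**Sections 2.6 and 2.7 are general text, and the inclusion criterion is the specific rule.** This softens the consent conflict. It does not remove it, because section 2.7 calls the participant's signature a prerequisite and makes no exception.

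**Eligibility does not depend on arm.** A reader might infer that the protocol sets different rules by arm. It does not. Criterion, teaching of the criteria and checklist are common; nothing makes the drug discussion a condition of entry; and excluding patients because they cannot manage it would go against the intent in section 7.1.1. All of that stands, so the point is a risk and not a stated difference. It has also been argued that study procedures simply means section 9, which bears that title. Section 7.1.2 does not say so, however, and section 9.3.4 itself contains the discharge procedure that differs by arm.

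**The direction is unknown.** This stands. Physicians keen to review medication might enrol more impaired patients, which would bias the result the other way.

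**Any criterion judged after allocation carries this risk.** True, but this one has an undefined yardstick whose natural reading may differ by arm, and that can be repaired cheaply.

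**Conclusion.** The inconsistency in the text is established: the synopsis and section 7.1 differ on patients who need assistance, sections 2.6/2.7 do not provide for the representative route, and section 7.1.2 is garbled. The passages must be reconciled.

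Different application of the criterion by arm is a reasonable inference from an undefined yardstick and post-allocation assessment by staff who know one arm only. The protocol does not state that it happens.

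The direction and size of any bias cannot be derived from the documents. On the assumed inputs above, with higher-risk patients excluded only from the intervention arm, the apparent hazard ratio with no true effect runs from about 0.97 to 0.83, against the planned 0.80. The upper scenario needs every impaired patient excluded in one arm and none in the other, which is extreme given section 7.1.1. A reader might infer that such a bias could exceed the whole planned effect, since the mean hazards at discharge give 1/1.3 = 0.77 in that scenario. That ignores the earlier loss of high-risk patients from the risk set. Over 182 days the figure is about 0.83, short of the planned effect. The point deserves correction before recruitment, but it does not by itself undermine the trial.

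**What to change.** 1. Use one wording of the cognitive exclusion in the synopsis, section 7.1.2 and checklist 11a, and remove the double negative.
2. Define it by tasks common to both arms: unable to provide the follow-up information at 1, 3 and 6 months, even with help from a relative or representative. Section 9.2.1 already allows relatives to be contacted for missing readmission data.
3. State that ability to take part in the medication discussion is not an eligibility criterion in either arm.
4. Reconcile sections 2.6 and 2.7 with the legal-representative route in section 7.1.1.
5. Count patients excluded for cognition in each ward and compare the counts by arm.

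The cost is a handful of text edits and one tally at screening. The small downside is that some intervention-arm patients will receive the medication discussion only through a relative or representative.

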### 7.2 Recruitment and Screening

For the adequate number of HPs and patients to be included in the trial see the sample size calculations in section 11.2.

Different hospitals – including but not limited to the Kantonsspital Baden, Kantonsspital Glarus, Kantonsspital Graubünden Chur (medical clinic), See-Spital Horgen, Spital Lachen, Spital Limmattal Schlieren, Spital Linth Uznach, Spital Männedorf, Kantonsspital Münsterlingen, Spital Muri, Spital Schwyz, Kantonsspital St. Gallen, Stadtspital Triemli Zurich, Stadtspital Waid Zürich, Kantonsspital Winterthur (polyclinic, surgical ward), Spital Zollikerberg, UniversityHospital Zurich (clinics for gastroenterology, pneumology and geriatrics) – will be contacted on the medical management level with detailed written information about the study and an invitation to participate. Should the targeted number of senior HPs be missed due to a low response rate, remainders will be sent out. If, on the other hand, the response exceeds the actual demand then a random selection of senior HPs will be drawn and the remaining respondents will be waitlisted to compensate for potential withdrawals.

The in-hospital recruitment of patients will be performed by HPs and/or nurses; a person responsible for recruitment will be defined in every clinic or ward. The patients' life expectancies and cognitive abilities will be assessed as part of the recruitment process. Patients will be recruited during four months or until the envisaged number of participants per cluster (senior HP) is reached, and follow up will last for six months for each patient.

### **7.3 Assignment to Study Groups**

Clusters will be assigned randomly to the two equally sized study arms as soon as the required number of clusters is reached. Given the relatively small number of clusters (see sample size calculation in section 11.2) and since we expect considerable variation in hospital types and clinic sizes, careful consideration needs to be given to balancing the covariates listed in section 5.2. For the sake of simplicity in a setting where there is no need for overly sophisticated sequential allocation algorithms and in order not to sacrifice too much randomness for balance, we chose the following randomization approach:

- In a first step, simple randomization (the “sample” command of the statistical software package “R”) will be used to generate N complete and fully random allocation schemes, imposing no constraints regarding balance except for equally sized study arms.
- In the second step, a set of  $n$  ( $\ll N$ ) schemes with the lowest imbalances will be identified, using a similar criterion as in minimization techniques (for an overview see for e.g. (30)), or, alternatively, all schemes with a criterion value below some prespecified cut-off value.
- Finally, exactly one of these remaining schemes will be selected at random.

The whole allocation process will be carried out by an independent person not involved in planning the trial nor delivering the intervention nor collecting outcomes. The investigators will only receive the final allocation scheme from the person responsible for allocation. This list of senior HPs belonging to the intervention and control groups, respectively, will be kept at the study center.

